### Sample Size and Power

Our feasibility study will involve 60 adults with SCD randomized to one of 2 groups: iMBSR or iLifeEd. Our primary outcome variables for this study are the feasibility and acceptability of the protocols. With 30 participants per group, we will be able to estimate within-group feasibility percentages (eg, the percentage of participants who find the program prospectively acceptable and the percentage of people who indicate adequate levels of satisfaction) with a margin of error of no larger than +18% or −18%. For intervention adherence, we will have 80% power for detecting a proportion of greater than 50% adherence if the true proportion of participants who complete all modules is 75%.

Our key secondary outcome variables for this study are the plasma Aβ_42_/Aβ_40_ ratio and plasma p-tau217, quantifying reduction in amyloid and tau pathology following training. We conducted sensitivity analyses to determine the effect size that we would need to observe to detect significant effects. Specifically, with 30 participants per group, we would need to observe a large effect size (Cohen *d*=0.74) to detect significant effects. Although there are, to our knowledge, no mindfulness-based interventions examining effects on plasma-based measures of amyloid and tau, prior work by one of the co-authors (EH) has demonstrated that 4 weeks of slow-paced breathing significantly decreases plasma Aβ_42^,^_ with a large effect size (Cohen *d*=0.81). As such, we are powered to detect the effect of our mindfulness intervention on plasma markers of amyloid. Other secondary variables of interest include behavioral and self-report measures of mind-wandering, including both laboratory- and EMA-based assessments of mind-wandering as well as the network strength of the DMN during the Gradual-Onset Continuous Performance Task. Given the pilot nature of the study, emphasis will be placed on the estimation of effect sizes and CIs for these effect sizes.

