### Study Procedures

Participants who meet the demographic criteria, along with criteria for the ECog Questionnaire, the T-MOCA, the IADL questionnaire, and MRI safety, are invited to the Clinical Neuroscience Laboratory at The Ohio State University for an initial in-person screening session. At this visit, visual acuity is assessed using the Snellen chart, and a blinded research assistant administers the UDS3-NB.

Participants meeting criteria for intact objective cognitive performance are then invited to a behavioral testing session at the Clinical Neuroscience Lab and a neuroimaging session at the Center for Cognitive and Behavioral Brain Imaging. During the behavioral session, a trained nurse from the Clinical Research Center at The Ohio State University collects the blood plasma sample, after which participants complete 2 behavioral measures of sustained attention and mind-wandering. As psychoaffective factors can influence perceived ratings of SCD, participants also complete a battery of questionnaires assessing stress (the Perceived Stress Scale [55]), depression (the Center for Epidemiologic Studies Depression Scale [56]), anxiety (the Beck Anxiety Inventory [57]), worry (the Penn State Worry Questionnaire [58]), quality of life (the World Health Organization Quality of Life–Brief [59]), and perceived racial discrimination (the Everyday Discrimination Scale [60]). We also administer the Motivation to Change Lifestyle and Health Behaviors for Dementia Risk Reduction [61] to quantify psychological and cognitive factors that influence engaging in health behaviors.

At the same session, participants receive training on EMA procedures and are provided with study-specific smartphones (Samsung Galaxy phones) to collect EMA data on mind-wandering, cognitive functioning, perceived stress, affect, and arousal for 5 days between sessions. Finally, structural and functional MRI data are collected at the neuroimaging session to quantify changes in the integrity of the DMN.

After completion of all assessment sessions, participants are randomized to either the iMBSR or the iLifeEd group with a 1:1 allocation ratio. All assessments will be readministered immediately following the 8-week intervention.

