Preprocessed fMRI data will then be parcellated using the Glasser functional atlas with 360 cortical regions and 19 subcortical regions [82,83]. The functional atlas will be transformed from MNI space to each participant’s native space. We will then extract the BOLD signal time courses from each of the 379 regions by averaging the signal across all voxels within each region. To compute the statistical dependence between BOLD signal across 2 nodes, we will first z-score each time series, compute their element-wise product, and then average this product to obtain the Pearson correlation coefficient between each pair of nodes. Calculating the Pearson correlation for all pairs of nodes will result in a 379×379 functional connectivity matrix for each participant, which will be used to compute the DMN connectivity.

Following the preprocessing of self-report, behavioral, and neuroimaging data, analyses will be conducted to determine intervention feasibility and acceptability. For preliminary effects on plasma biomarkers of AD pathology, behavioral and neural metrics of mind-wandering, and other secondary outcomes, we will fit linear mixed models to account for within-subject correlations arising from measuring each subject at 2 time points. In these models, emphasis will be placed on estimating effect sizes and CIs, rather than on hypothesis testing. As we are including adults with SCD based on self-reported concerns, we will also conduct sensitivity analyses using the total score on the Penn State Worry Questionnaire [58] to examine whether feasibility, acceptability, and preliminary effects differ as a function of worry scores within the current sample.

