In addition to examining feasibility and acceptability, this study will examine the preliminary effects of mindfulness practice on amyloid and tau pathology. The deposition of these proteins in the densely connected nodes of the DMN is a characteristic hallmark of AD [107,108]. Early aggregation of amyloid has been observed in anterior midcortical structures, such as the medial orbitofrontal gyrus and the anterior cingulate cortex, as well as in posterior midcortical structures, including the posterior cingulate cortex and the precuneus. Tau pathology is known to spread in a prion-like manner, beginning in the transentorhinal cortex and progressing to the perirhinal cortex, hippocampus, limbic areas, and, eventually, the association cortices [109-112]. The spatial affinities of Aβ and tau-based tangles for DMN regions, which also appear to support the prophylactic benefits of mindfulness meditation [26-31], provide the scientific rationale for this RCT. We hypothesize that mindfulness training will facilitate present moment awareness and reduce mind-wandering in daily life, thereby strengthening DMN connectivity and exerting downstream cascading effects on amyloid and tau pathology.

AD pathology in this study will be quantified using the recently validated plasma-based biomarkers of Aβ and tau [113-117]. Emerging evidence demonstrates that low plasma Aβ (Aβ_42_/Aβ_40_) levels are associated with higher brain amyloid deposition as measured using PET imaging [118-120]. Although high levels of p-tau217 show a positive association with amyloid PET data, growing evidence also suggests that plasma p-tau217 is even more closely associated with brain tau deposition, particularly in later disease stages [115,121,122]. Importantly, these plasma-based measures were recently validated in a multiethnic community study of 300 participants that included 46% non-Hispanic White participants and 54% participants from other ethnoracial groups [123]. The iMBT clinical trial will provide the first test of whether online mindfulness training can reduce amyloid and tau pathology in adults at risk for AD.

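### The claim to be powered for plasma amyloid rests on an effect size for Aβ42 alone and establishes no power for the named outcome, the Aβ42/Aβ40 ratio

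*Protocol article*

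**What the plan says.** All references are to the protocol article.

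- **Outcome.** Sample Size and Power states: "Our key secondary outcome variables for this study are the plasma Aβ_42_/Aβ_40_ ratio and plasma p-tau217". The section on plasma-based biomarkers again names the ratio as the measure of amyloid pathology. No other amyloid marker is named as an outcome.
- **Sensitivity figure.** "with 30 participants per group, we would need to observe a large effect size (Cohen *d*=0.74) to detect significant effects". Alpha, sidedness and power are not given for this figure.
- **Supporting evidence.** The authors know of no mindfulness trial with plasma amyloid or tau outcomes. They cite earlier work in which four weeks of "slow-paced breathing significantly decreases plasma" Aβ42, with d=0.81.
- **Conclusion drawn.** "As such, we are powered to detect the effect of our mindfulness intervention on plasma markers of amyloid".
- **Meaning of the ratio.** The Discussion says that low plasma Aβ42/Aβ40 "levels are associated with higher brain amyloid deposition as measured using PET imaging".
- **Attrition.** Primary Outcomes counts attrition of up to 25% as compatible with high feasibility.
- **Analysis.** For the biomarkers, Data Management and Analysis says that "emphasis will be placed on estimating effect sizes and CIs, rather than on hypothesis testing".

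**The concern.** The argument changes endpoint between premise and conclusion. The premise concerns the concentration of one peptide, Aβ42. The conclusion is applied to amyloid markers in this trial, where the only one named is a ratio with Aβ42 as its numerator. An effect size for the numerator says nothing definite about the ratio unless the change in the denominator is known, and it is not given.

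The direction makes the gap more than formal. The precedent is a fall in Aβ42, while the Discussion associates a low ratio with more brain amyloid. A fall in the numerator is therefore not, in itself, evidence of benefit on the named outcome.

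The precedent also comes from a different intervention of half the length (4 weeks against 8), and the article does not say whether its d is a between-group or a within-group effect. Only a between-group d can be compared with 0.74.

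At stake is how the result will be read. After a claim of adequate power, an interval for the ratio that includes zero may be taken as evidence that the programme has no effect, when the trial may have had little chance of detecting one.

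**Working it through.** **Inputs.** 30 per group (Sample Size and Power); 1:1 allocation (Study Procedures: "participants are randomized to either the iMBSR or the iLifeEd group with a 1:1 allocation ratio"); detectable d=0.74 and cited d=0.81 (Sample Size and Power); tolerated attrition 25% (Primary Outcomes). Assumed, because not stated for this figure: two-sided alpha 0.05, 80% power, two-sample t test.

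**1. Reproduce the plan's figure.** By the normal approximation, d = (1.960 + 0.842) × √(2/30) = 0.723. By the noncentral t distribution with 58 degrees of freedom, d = 0.736, which rounds to the stated 0.74; power at d=0.74 is 80.5%. One-sided 0.05 would give 0.65 and two-sided 0.025 would give 0.81, so the assumed settings are the ones that match. The figure is the true effect giving 80% power. The smallest observed d reaching significance is 2.002 × √(2/30) = 0.52, so describing 0.74 as the effect that must be observed is loose.

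**2. Power at the cited effect, for Aβ42 itself.** Noncentrality = d × √(n₁n₂/(n₁+n₂)).

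- 30 and 30: 0.81 × √15 = 3.14; power 87%.
- 25% attrition, assumed even across arms: 60 × 0.75 = 45, or 22 and 23. Noncentrality = 0.81 × √(22 × 23/45) = 2.72; power 76%.
- Detectable d at 80% power: 0.845 with 23 per arm and 0.865 with 22 per arm. Both exceed 0.81.

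So the step from 0.81 > 0.74 to adequate power is numerically right for Aβ42 with no dropout, and reverses at the attrition the plan accepts.

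**3. Carry the Aβ42 result to the ratio.** If Aβ42 changes by the fraction x and Aβ40 by y, the ratio changes by (1+x)/(1+y) − 1. The document gives neither, so these values are illustrative only:

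| Aβ42 | Aβ40 | Ratio | Reading under the Discussion |
|---|---|---|---|
| −10% | 0% | −10.0% | unfavourable |
| −10% | −5% | −5.3% | unfavourable |
| −10% | −10% | 0.0% | none |
| −10% | −15% | +5.9% | favourable |

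The same fall in Aβ42 fits every sign of change in the ratio.

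**4. Power for the ratio.** No single figure can be computed, because there is no effect size or SD for the ratio. Over an assumed range of true d, with 30 per arm:

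| True d | 0.2 | 0.3 | 0.4 | 0.5 | 0.6 | 0.74 |
|---|---|---|---|---|---|---|
| Power | 12% | 21% | 33% | 48% | 63% | 80% |

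**The case against.** The best defence is that this is a Stage I pilot. The primary outcomes are feasibility and acceptability, with their own precision and power statements. Biomarker effects are called preliminary, efficacy is left to later stages, and the analysis puts its weight on estimation. Correcting the sentence changes no sample size, assay or model. All of this stands and limits the severity. It does not rescue the sentence, which is an affirmative statement whose premise does not support it, and not a detail left to an analysis plan.

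Several stronger readings are tempting and should not be made.

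- **That the cited result predicts a lower or unchanged ratio.** A reader might infer this from the fall in Aβ42. It does not follow: if Aβ40 falls proportionally more, the ratio rises, and the document is silent on Aβ40.
- **That no direction of benefit is declared.** No single sentence says so, but the outcomes are described as measuring reduced pathology, the ratio is the measure of amyloid pathology, and the Discussion ties a low ratio to more amyloid. Together these imply that a higher ratio is benefit. Nothing in the text calls a lower ratio a success.
- **That power is also wrongly claimed for p-tau217.** The sentence is confined to amyloid.
- **That the claim contradicts an estimation-only analysis.** The plan speaks of emphasis, which does not exclude testing. The Discussion's statement that the trial "will provide the first test of whether online mindfulness training can reduce amyloid and tau pathology" sits uneasily beside that emphasis, but it is a matter of tone.

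**Conclusion.** The concern holds in a limited form: the statement of being powered for plasma amyloid is unsupported as written. The sensitivity figure of 0.74 is correct. The error is in transferring d=0.81 from Aβ42 to the Aβ42/Aβ40 ratio. Power for the ratio is unknown, and it would be 12% to 48% if the true standardised effect lay between 0.2 and 0.5 (an assumed range). For Aβ42 itself, power at d=0.81 is 87% with complete data and about 76% at 25% attrition.

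These figures assume a two-sample comparison at two-sided 5%, attrition split evenly, and a cited d that is a between-group effect. The planned linear mixed model could do somewhat better or worse depending on the correlation between the two time points, which the article does not give. That does not affect the main conclusion, which rests on the change of endpoint.

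Severity: should-fix. The outcome is secondary, and the primary feasibility and acceptability conclusions are unaffected.

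**What to change.** 1. In Sample Size and Power, delete the sentence claiming power for amyloid markers. Give only the sensitivity result with its conditions: a true effect of d=0.74 is detectable with 80% power at two-sided 5% if 30 per arm are analysed, rising to about 0.85 to 0.87 at 25% attrition.
2. Add that no effect size is available for the Aβ42/Aβ40 ratio. If the breathing study is kept as background, say that its effect concerns Aβ42 and state whether it is between-group or within-group.
3. State explicitly, in line with the Discussion, that a higher ratio is the favourable direction.
4. Report Aβ42 and Aβ40 beside the ratio, so that a change in it can be traced to its numerator or denominator. Both are needed to form the ratio, so no extra assay is required.

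The cost is a few sentences and two rows in the biomarker table; the stated power becomes less favourable. According to Results, data analysis starts only after all participants have finished, so the direction can still be put on record before results are known.

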### Study Procedures

Participants who meet the demographic criteria, along with criteria for the ECog Questionnaire, the T-MOCA, the IADL questionnaire, and MRI safety, are invited to the Clinical Neuroscience Laboratory at The Ohio State University for an initial in-person screening session. At this visit, visual acuity is assessed using the Snellen chart, and a blinded research assistant administers the UDS3-NB.

Participants meeting criteria for intact objective cognitive performance are then invited to a behavioral testing session at the Clinical Neuroscience Lab and a neuroimaging session at the Center for Cognitive and Behavioral Brain Imaging. During the behavioral session, a trained nurse from the Clinical Research Center at The Ohio State University collects the blood plasma sample, after which participants complete 2 behavioral measures of sustained attention and mind-wandering. As psychoaffective factors can influence perceived ratings of SCD, participants also complete a battery of questionnaires assessing stress (the Perceived Stress Scale [55]), depression (the Center for Epidemiologic Studies Depression Scale [56]), anxiety (the Beck Anxiety Inventory [57]), worry (the Penn State Worry Questionnaire [58]), quality of life (the World Health Organization Quality of Life–Brief [59]), and perceived racial discrimination (the Everyday Discrimination Scale [60]). We also administer the Motivation to Change Lifestyle and Health Behaviors for Dementia Risk Reduction [61] to quantify psychological and cognitive factors that influence engaging in health behaviors.

At the same session, participants receive training on EMA procedures and are provided with study-specific smartphones (Samsung Galaxy phones) to collect EMA data on mind-wandering, cognitive functioning, perceived stress, affect, and arousal for 5 days between sessions. Finally, structural and functional MRI data are collected at the neuroimaging session to quantify changes in the integrity of the DMN.

After completion of all assessment sessions, participants are randomized to either the iMBSR or the iLifeEd group with a 1:1 allocation ratio. All assessments will be readministered immediately following the 8-week intervention.

### Randomization and Blinding

The study biostatistician (RA) generated the randomization sequence using a block size of 4 with stratification by sex. The project coordinator (EKG) received concealed envelopes for the 2 strata and is responsible for assigning eligible participants to one of the 2 groups. The project coordinator, the study facilitators, and the study biostatistician are the only team members unblinded to group assignment. All personnel conducting assessments, behavioral or neuroimaging, will remain blind to group assignment.

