## Results

This study was funded by the National Institute on Aging in April 2024. Phase I focused on iterative development of the 2 programs based on focus group feedback. Recruitment for the Phase II RCT (iMBT) began on June 13, 2025, and is ongoing. As of December 1, 2025, we have 31 participants randomized into the study: 15 participants have been randomized to the iMBSR group, and 16 participants have been randomized to the iLifeEd group. We anticipate that recruitment will end in September 2026, with all 60 participants randomized by that date. Although data analyses will begin after all participants have completed the intervention and assessment sessions, all analysis scripts have been finalized, and data reduction and processing are ongoing. We expect to complete the processing and analysis of the primary outcome variables by March 2027, with a targeted manuscript submission date of June 2027.

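### A constant, disclosed block size of 4 within each sex, used by an unblinded envelope-holder, lets about a third of allocations be deduced in advance; selection bias is possible, not demonstrated.

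*Protocol article*

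**What the plan says.** Protocol article, Randomization and Blinding: the biostatistician "generated the randomization sequence using a block size of 4 with stratification by sex". One size is given. The section mentions neither variation in block size nor release of assignments by anyone outside the team.

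The same section says that the project coordinator "received concealed envelopes for the 2 strata and is responsible for assigning eligible participants to one of the 2 groups". On blinding it states: "The project coordinator, the study facilitators, and the study biostatistician are the only team members unblinded to group assignment". It adds: "All personnel conducting assessments, behavioral or neuroimaging, will remain blind to group assignment".

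Study Procedures gives the ratio ("randomized to either the iMBSR or the iLifeEd group with a 1:1 allocation ratio") and the timing ("After completion of all assessment sessions, participants are randomized").

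Sample Size and Power sets the total: "Our feasibility study will involve 60 adults with SCD randomized to one of 2 groups". Results reports the position at December 1, 2025, with recruitment continuing: "15 participants have been randomized to the iMBSR group, and 16 participants have been randomized to the iLifeEd group".

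**The concern.** Sealed envelopes hide the next assignment only if it cannot be worked out from earlier ones. With one known block size, past assignments within a stratum reveal part of what follows. The only stratifier is sex, so anyone who knows a participant's sex knows which sequence applies. The coordinator's role combines the three ingredients: custody of the envelopes, the act of assignment and sight of earlier assignments.

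If a person who can foresee the next arm also has some say over who is randomized when, the mix of participants in the two arms can drift apart. The primary outcomes listed in the article include attrition, acceptability, satisfaction and module completion, all of which plausibly depend on motivation. Each arm has 30 people, so a shift of three participants moves a within-arm percentage by 3/30 = 10 points. The between-group estimates for plasma biomarkers and mind-wandering would be exposed in the same way. Blinded assessors protect measurement; they do not correct selection at entry.

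**Working it through.** The article states no predictability figure, so there is none to reproduce.

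**Inputs.** Block size 4 and two sex strata (Randomization and Blinding); 1:1 ratio, hence 2 + 2 per block (Study Procedures); 60 participants (Sample Size and Power); 31 randomized at December 1, 2025 (Results, 15 + 16). The sizes of the sex strata are not given, so every split of 60 was examined.

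**One complete block.** The six orders of two and two are equally likely.

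| Position | Probability that it is certain | Probability that the best guess is right |
|---|---|---|
| 1 | 0 | 1/2 |
| 2 | 0 | 2/3 |
| 3 | 1/3 (first two the same) | 1/3 × 1 + 2/3 × 1/2 = 2/3 |
| 4 | 1 | 1 |

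- Certain: (0 + 0 + 1/3 + 1)/4 = 33.3%, or 4/3 allocations per block.
- Best guess right: (1/2 + 2/3 + 2/3 + 1)/4 = 70.8%, against 50% under full concealment.

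**All 60 participants, last block possibly incomplete.**
- Both strata divisible by 4: 15 blocks × 4/3 = 20.0 (33.3%).
- Strata leaving remainders 1 and 3: 14 × 4/3 + 1/3 = 19.0 (31.7%).
- Strata each leaving remainder 2 (for example 30/30): 14 × 4/3 = 18.7 (31.1%).

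The range is therefore 31.1% to 33.3% for any split. Applied to the 60 − 31 = 29 outstanding at the stated date, this is 29 × 0.311 = 9.0 to 29 × 0.333 = 9.7 allocations.

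**Effect of varied block sizes.** This was simulated for a guesser who knows the set of sizes and all past assignments, but not the size of each block.

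| Block sizes | Certain, 30 per stratum | Best guess, 30 per stratum | Certain, run of 15 | Best guess, run of 15 |
|---|---|---|---|---|
| 4 only | 31.1% | 70.0% | 28.8% | 68.9% |
| 4 and 6 | 5.8% | 68.9% | 6.0% | 67.6% |
| 4, 6 and 8 | 2.5% | 67.5% | 2.4% | 66.2% |

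Certain knowledge nearly disappears. The best-guess rate falls by 1.1 to 1.3 points with sizes 4 and 6, and by 2.5 to 2.7 points with 4, 6 and 8.

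**Imbalance.** The largest difference between arms within a sex, if the last block is incomplete, is half its size: 2 for a block of 4, 3 for 6 and 4 for 8. An abandoned open block of 4 can add 2 more, so 5 with sizes 4 and 6, or 6 with 4, 6 and 8. Because 31 is odd, at least one sex had an open block at the stated date.

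**The case against.** A reader might infer that the coordinator knows a third of the assignments and that the feasibility results will be biased. The article supports neither step. Deduction requires someone to track block position within each sex, and nothing shows that anyone does. The article gives the coordinator only the assignment of eligible participants. It does not say who screens, consents or schedules, and a condensed article may leave that to the full protocol.

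Existing safeguards also narrow the route. Eligibility rests on numerical cutoffs (ECog, T-MOCA, IADL and the neuropsychological criteria). A blinded research assistant gives the in-person battery. Randomization follows all baseline sessions, so little room remains to turn away a marginal candidate. Enrolment of 60 is a trial-wide criterion that moving people between arms does not change directly. The other primary criteria are fixed thresholds, the between-group analyses emphasize estimation over testing, and causal claims about efficacy against the control are left to future studies.

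Two further inferences should be avoided. The article does not describe participants as open-label; its blinding statement covers team members only. The 29 outstanding is a count at one date, and the number still to be randomized when a change could take effect is unknown.

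These objections stand, and they limit the point to a possible bias. They do not remove the predictability: cutoffs and completed baselines still leave the order and timing in which eligible people are randomized, and the article states no separation of those duties from assignment. A constant block of 4 does keep small strata closely balanced, but varied blocks give up little of that.

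**Conclusion.** The point holds as a weakness of the stated allocation procedure. Between 31% and 33% of allocations can be deduced with certainty by someone who knows the block size and follows each sex stratum, and the article gives one unblinded person both the envelopes and the assignments. The figure assumes 2 + 2 blocks run in sequence and complete knowledge of past assignments within each sex; it does not depend on the sex split.

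Whether this has affected, or will affect, who enters each arm cannot be judged from the article. No size can be put on any bias. In a Stage I feasibility trial this is a low-cost improvement worth making while recruitment is open, and not evidence that the results are compromised.

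**What to change.** For participants not yet randomized:

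1. Let the open block in each sex run to its end. At most three allocations per sex then remain under the old scheme.
2. Have the biostatistician, who is already unblinded, issue a new list per sex with randomly varied block sizes, for example 4 and 6. Do not disclose the sizes or their order to the coordinator, and publish them only after the last randomization.
3. Record a time stamp for confirmed eligibility and completed baseline before each envelope is opened. The sequence of events is already in Study Procedures; the auditable record is the addition.

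**Cost.** A new list, new envelopes and a short amendment, with no extra staff. The possible final imbalance within each sex rises from 2 to 3 with sizes 4 and 6, or to 4 with 4, 6 and 8, and by 2 more if an open block is abandoned instead of finished.

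**Limit.** The gain is in removing certain knowledge (to about 6%, or about 2% with 4, 6 and 8). An informed guess would still be right about two times in three, because the same unblinded person would still see past assignments.
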